#### Arm 1: G4H (The Experimental Group)

G4H is a manualized group intervention that targets social group memberships with the aim of improving well-being [17], as discussed in the introduction.

The G4H intervention consists of five 90-minute sessions that aim to provide participants with the knowledge and skills they need to effectively manage their social group memberships and identities. Each of the 5 intervention sessions pertains to 1 module. Each module integrates exercises and discussions from the G4H workbook targeting various aspects of group dynamics as outlined in the SIAH and SIMIC frameworks. In brief, the first module “schooling” provides psychoeducation about the importance of social group memberships for health; the second module “scoping” supports the participants in exploring their social identities and networks; the third module “sourcing” aims at strengthening the social identities that are valued by the participant; the fourth module “scaffolding” supports making a social action plan to establish new valued group memberships; and finally, the fifth module “sustaining” aims at revisiting the intervention, discussing any potential difficulties, and encouraging the maintenance of group memberships [17]. A detailed description of the modules can be found in the G4H manual [32].

At the UH, the G4H group size can vary between 4 and 9 university students. The groups are mostly organized face-to-face, although some groups meet entirely remotely. The students earn 2 European Credit Transfer and Accumulation System (ECTS) credits for completing the G4H intervention.

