#### Arm 3: TBWS (Active Comparator 2)

TBWS is an optional, 7-week online intervention course available for all UH students that aims to foster well-being and study skills. The course protocol has been described in detail earlier by Asikainen and Katajavuori [34]. The course is based on the principles of acceptance and commitment therapy [35] and aims to promote psychological flexibility. In addition, it aims to support study skills such as time management. The course takes place on an online learning platform (Moodle), and the students earn 3 ECTS credits for completing it. This course progresses weekly and has 6 central themes, including an introduction to the themes, individual work in practicing psychological flexibility and study skills, and weekly peer group discussions. The peer group work is an important part of the intervention and lasts throughout the course. In the peer groups, there are about 5 students in each group, and the groups remain the same throughout the course. Acceptance and commitment therapy–based interventions have been shown to support well-being among university students [36], and previous studies have suggested that this course can improve students’ well-being and studying in several ways [37,38]. Thus, participating students have the potential to benefit from this intervention in terms of increased well-being.

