#### Secondary Outcomes

The secondary outcomes are active group memberships, mental well-being, general well-being, anxiety, social anxiety, academic performance, health-related quality of life, use of social and health care services, intervention costs, and cost-effectiveness of the intervention (refer to Table 1 and Multimedia Appendix 1 for details).

To assess participants’ academic performance, data will be retrieved from the UH student register (Sisu student information system). Academic performance is determined by 3 outcome variables: overall accumulated study credits, the grade point average (GPA) of the study credits and the weighted GPA. When determining the weighted GPA, only completed studies that have been assessed on a numeric scale (from 1 to 5) are considered, as some courses accumulate study credits but are graded only as passed or failed. Weighted GPA is determined by the grades of each course weighted by the number of credits gained for it. The academic performance data are collected from 2 time periods: a 1-year period before and a 1-year period after starting the assigned intervention (baseline, week 1).

Cost-effectiveness analyses will apply a societal perspective by including intervention costs as well as university students’ health and social services costs. For the cost-effectiveness analyses, the facilitators will provide information on the time used for planning, executing, and assessing the sessions to evaluate the costs of the G4H intervention. Furthermore, the students in all trial arms fill out 2 questionnaires before the intervention, immediately after the intervention, and at 3-month follow-up (Table 1). The questionnaires measure health-related quality of life and self-reported use of health and social services (Table 1). The use of health and social services will be monetarized using Finnish national unit costs [62].

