#### Background Variables

In addition to the outcome measures described above, survey data on the participants’ background are gathered to account for them in the analyses and to examine their potential in moderating or mediating the effectiveness of the intervention (Table 1 and Multimedia Appendix 1). The participant background questionnaire includes questions on sociodemographic characteristics (refer to Table 1 for details), experienced social support, organized studying, and situational intrinsic and extrinsic motivation. Readiness to attend the intervention is enquired by a set of readiness rulers adapted from Miller and Rollnick [56]. Furthermore, data are gathered from the UH registries, including information on study rights (faculty, degree programs, and fields of study) and their starting years, active and passive registration, and completed degrees.

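### The RQ2 credit outcome, as defined, counts the credits awarded for completing G4H (2 ECTS) and TBWS (3 ECTS), building in a small difference from controls

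*Protocol article*

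**What the plan says.** The Secondary Outcomes section of the protocol article defines academic performance by three variables: "overall accumulated study credits, the grade point average (GPA) of the study credits and the weighted GPA". The data come from the university's student register and cover "a 1-year period before and a 1-year period after starting the assigned intervention", with the start placed at baseline, week 1. The seven-week intervention period therefore lies inside the second window.

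The arm descriptions state what completion earns:

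- Arm 1 (G4H): "The students earn 2 European Credit Transfer and Accumulation System (ECTS) credits for completing the G4H intervention".
- Arm 3 (TBWS): "the students earn 3 ECTS credits for completing it".
- Arm 2 (SPGs): the section is silent on credits.
- Arm 4 (controls): students not currently in any of the university's group interventions for study skills or well-being.

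The only rule on which courses count is the restriction to numerically graded studies, and it is stated for the weighted GPA alone. In the Aim and Objectives section, all active interventions are hypothesised to improve academic performance relative to controls.

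**The concern.** The article fixes the source (the register), the variable (all accumulated credits) and the window (from the first week of the intervention). Taken together, these count the credit for attending the intervention as part of the outcome that the intervention is meant to improve. The amount differs by arm, so it does not cancel in the comparisons.

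At stake is the RQ2 comparison with controls. Two of the three active arms can show more credits without any change in how students study. The comparisons of G4H with TBWS and with SPGs may also be shifted. The planned inverse propensity weighting and double robust estimators deal with selection into arms and with dropout. They cannot remove a difference that arises after baseline inside the outcome itself.

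**Working it through.** The article gives no sample size, power or effect for study credits, so there is no figure of its own to reproduce.

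**Inputs from the article.** Credits on completion: 2 (G4H) and 3 (TBWS). Arm sizes at the first data freeze (Study Status): G4H 155, TBWS 216, controls 203. The analysis is by intention to treat, so non-completers are included and earn no intervention credit.

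**Assumptions, not in the article.** SD of one-year credits 20 (range 15 to 25); two-sided alpha 0.05; unadjusted comparison of two means; completion rate p of 100%, 80% or 60%; zero credits for controls during the window; no substitution for other courses.

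**Step 1: built-in mean difference = credits × p.**

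- G4H versus control: 2p, so 2.0, 1.6 or 1.2 credits.
- TBWS versus control: 3p, so 3.0, 2.4 or 1.8 credits.
- G4H versus TBWS: 2p(G4H) − 3p(TBWS). With full completion in both arms this is −1 credit, against G4H. Unequal completion moves it either way.
- G4H versus SPGs: up to 2 credits in favour of G4H, only if SPGs award none (assumption).

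**Step 2: chance of rejection with no real effect.** z = difference / [SD × √(1/n₁ + 1/n₀)]; P(reject) = Φ(z − 1.96) + Φ(−z − 1.96).

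- G4H, SD 20, p = 100%: standard error = 20 × √(1/155 + 1/203) = 2.13; z = 2/2.13 = 0.94; P = 0.155.
- TBWS, SD 20, p = 100%: standard error = 20 × √(1/216 + 1/203) = 1.96; z = 3/1.955 = 1.53; P = 0.335.

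| Completion | SD | G4H vs control | TBWS vs control |
|---|---|---|---|
| 100% | 15 | 24% | 53% |
| 100% | 20 | 16% | 34% |
| 100% | 25 | 12% | 23% |
| 80% | 15 | 17% | 37% |
| 80% | 20 | 12% | 23% |
| 80% | 25 | 9% | 17% |
| 60% | 15 | 12% | 23% |
| 60% | 20 | 9% | 15% |
| 60% | 25 | 7% | 11% |

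The nominal value is 5%. In standardised terms the full-completion difference at SD 20 is 2/20 = 0.10 for G4H and 3/20 = 0.15 for TBWS.

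**Step 3: after the fix.** With the intervention credits removed, the built-in difference is 0 in every comparison and the rejection rate returns to 5%.

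**The case against.** The strongest reply has four parts.

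- *The net gain is not fixed.* A student may take a 2- or 3-credit course in place of another. Credit requires completion, and the analysis is by intention to treat. Controls are outside the interventions only at enrolment, and the caption of the recruitment flow chart records students who had already taken part, sometimes in another arm, so some controls may earn the same credits within the year. All of this stands. A reader might infer that G4H and TBWS must beat controls by 2 and 3 credits; the documents support those figures only as upper bounds.
- *Silence on SPG credits is not zero.* This stands. The shift between G4H and SPGs is conditional.
- *The size rests on assumed inputs.* The SD, alpha and completion rates are not in the article, and the planned model is not an unadjusted two-sample test. This also stands, and the percentages are illustrations. The existence and direction of the gross credit do not depend on them.
- *Which course codes to drop is a derivation rule that an article may leave to a fuller document.* This carries less weight. The article does not merely omit a detail: the source, variable and window that it states include these credits.

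Two further readings are tempting but unsupported. One is that both GPA measures are contaminated: nothing says that G4H or TBWS is graded numerically, and the weighted GPA already leaves out pass/fail courses. The other is that Table 2 (study years from 0 in every arm; mean 4.6 in SPGs against 1.6 to 1.9 elsewhere) shows empty pre-intervention years for entrants or more graduations among SPG students. The variable is years in the current degree, so a zero can belong to a student with credits from an earlier degree. A long duration may reflect delayed study, since SPG themes include returning after a break.

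**Conclusion.** The point holds for accumulated credits. As defined, the outcome includes the treatment's own credits. The mean shift against controls is at most 2 credits (G4H) and 3 credits (TBWS), scaled by completion and reduced by any substitution. At an assumed SD of 20 (15 to 25), this raises the chance of a significant result under no real effect from 5% to at most 16% (12 to 24%) for G4H and 34% (23 to 53%) for TBWS. At 60% completion and SD 20 the values are about 9% and 15%. Here, at most refers to completion and substitution; a smaller SD would raise the figures.

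The defect should be fixed, but its reach is limited to one of three variables for one secondary outcome. Loneliness, depression and the cost-effectiveness analyses are not affected.

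**What to change.** Define the RQ2 credit outcome as accumulated credits excluding any awarded for G4H, TBWS or SPG participation. Apply the rule in all four arms and in both one-year windows, so that students who took one of these courses earlier, or who join one later, are treated alike. State whether SPGs award credits. Extend the exclusion to GPA only if any of these courses is graded numerically. Report the unfiltered total as a sensitivity analysis, since the credits are real entries in the student's record.

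The cost is a filter on course codes. The weighted GPA already requires grades and credits by course, so no new kind of data is needed. The Study Status section schedules the RQ2 analyses for 2026 to 2027, so the rule can be set down before they are run.

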#### Other Outcomes

Other outcome measures include the participant’s identification with the intervention group, attendance, and mood, as well as facilitators’ fidelity to the intervention manual, and both the participant’s and facilitator’s evaluations of the working alliance (Table 1 and Multimedia Appendix 1). These measures are used to examine their potential in moderating or mediating the effectiveness of the intervention. Fidelity to the intervention manual is measured with a questionnaire detailing how well the facilitators covered the core themes of each intervention session. Each facilitator pair fills in the questionnaire immediately after each intervention session. This questionnaire is the same as used by the previous study that assessed program adherence to the G4H [33] .

#### Background Variables

In addition to the outcome measures described above, survey data on the participants’ background are gathered to account for them in the analyses and to examine their potential in moderating or mediating the effectiveness of the intervention (Table 1 and Multimedia Appendix 1). The participant background questionnaire includes questions on sociodemographic characteristics (refer to Table 1 for details), experienced social support, organized studying, and situational intrinsic and extrinsic motivation. Readiness to attend the intervention is enquired by a set of readiness rulers adapted from Miller and Rollnick [56]. Furthermore, data are gathered from the UH registries, including information on study rights (faculty, degree programs, and fields of study) and their starting years, active and passive registration, and completed degrees.

#### Facilitators’ Characteristics

To investigate how facilitators’ individual professional and personal characteristics may predict the intervention process and effectiveness, G4H facilitators complete self-report measures both before and during the interventions (Table 1 and Multimedia Appendix 1). Before initiating the intervention, facilitators complete questionnaires related to personality traits, attachment style, and self-experiences in close personal relationships. After the third session, the facilitators report experiences of their current skillfulness, difficulties, and emotions in group work.

### Statistical Analyses

We will conduct our analysis following the intention-to-treat principle, including all participants regardless of whether they completed the intervention.

The change in the outcome variables over time will be analyzed with linear mixed-model analyses due to the hierarchical data structure. Information criteria are used to assess model fit and determine the appropriate model structure. Mixed effects models can also be fitted for participants with missing data from one or more time points. If needed, other appropriate imputation methods, such as multivariate imputation by chained equations [63], will be used. For this reason, the number of participants included in the analyses is likely to be higher than the number of participants providing data at the last follow-up.

We will explore with logistic regression analyses whether background characteristics and baseline psychiatric symptoms predict study dropout, and necessary means to account for any systematically missing data will be taken. We aim to show that the missing observations of the outcome variable, due to dropout, are conditionally independent from the observed values of the outcome variable given our model for dropping out from the study. If needed, inverse propensity score weighting is carried out so that the treatment effects are conditionally independent from the treatment group assignments and from differing dropout rates given the propensity scores. We consider individuals’ selection into different study groups (arms) under the stable unit treatment value assumption based on their background characteristics, given that we have access to an extensive dataset. The selection of individuals into groups is accounted for by making the estimators double robust, which is a well-known approach to adjust for selection into groups based on background characteristics in model-based estimates [64,65]. This ensures that our results are unbiased and consistent estimators of the treatment effects. Potential effects of the COVID-19 pandemic on the stability and change in students’ well-being will be inspected and considered in the analyses if necessary.

All models will be inspected for normality of residuals, homoscedasticity, and multicollinearity. The outcome variables will be transformed to attain normality if needed. Appropriate interaction terms are added for further subgroup analyses. Potential mediator (eg, therapeutic alliance, motivation, and model fidelity) and moderator (eg, participant and facilitators' background) effects will be inspected in additional mediation and moderation analyses.

In the case of missing questionnaire items, within-person imputation is carried out for responses when less than 50% of the answers are missing per scale (the within-person average of the existing items is imputed to the missing responses). We acknowledge that this procedure may decrease the within-person variation in the data. However, as we discuss later, the prevalence of item nonresponse in the dataset is low.

We will take appropriate measures to balance between Type I and Type II error in the reporting of analyses results. If needed, we will use methods to account for multiple testing such as false discovery rate or new eigenvalue-based methods that provide a more accurate adjustment for nonindependence among tests [66].

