#### Arm 2: SPGs (Active Comparator 1)

The UH study psychology team organizes group interventions for various challenges related to studying for bachelor’s and master’s students. The SPGs offer client-centered peer support facilitated mostly by 2 study psychologists (some individual sessions may have only 1 facilitator). The recurring themes in the SPGs include challenges with attention, independent studying, scientific writing, and support for re-entering the studies after a break. The structure of the different thematic groups is similar—short presentations, group discussions, practices, and homework. These groups are implemented mostly as face-to-face meetings; however, in some groups, part of the meetings are conducted face-to-face and part as remote meetings. One group typically lasts for a study period and comprises five to six 90‐105 minute sessions. The typical group size ranges from 10 to 12 students. The interventions have potential in supporting study skills and the challenges of initiating study tasks, identifying and normalizing unpleasant thoughts and emotions related to studying, and acknowledging the role of one’s individual situation and well-being in study planning. The study psychologists’ work is bound by the legal and ethical requirements for licensed psychologists in Finland, overseen by the National Supervisory Authority for Welfare and Health (Valvira).

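### The group level of the mixed model is left open to selection by information criteria, although three of the four arms are delivered in groups

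*Protocol article*

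**What the plan says.** The Statistical Analyses section states that change over time "will be analyzed with linear mixed-model analyses due to the hierarchical data structure". It does not name the levels of that hierarchy. The next sentence reads: "Information criteria are used to assess model fit and determine the appropriate model structure". It names neither the criterion nor the candidate structures, and holds no term back from the choice.

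The Interventions section describes how each arm is delivered:

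- G4H: "the G4H group size can vary between 4 and 9 university students", each group led by two student facilitators.
- SPG: "The typical group size ranges from 10 to 12 students", mostly led by two study psychologists, with peer support as part of the content.
- TBWS: in the peer groups, "there are about 5 students in each group, and the groups remain the same throughout the course".
- Controls: no group intervention.

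The same analysis section plans inverse propensity weighting if needed and doubly robust estimation, and considers "selection into different study groups (arms) under the stable unit treatment value assumption based on their background characteristics". It says nothing on how the variance of those estimators allows for delivery groups. The Sample Size section mentions no clustering.

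**The concern.** Students treated in the same group share facilitators, peers and sessions, so their outcomes may be correlated. Controls have no such correlation. This is a partially nested design, and the group level follows from how treatment is delivered. A fit statistic is a poor guide to whether it belongs in the model. With small groups and a small ICC, the gain in likelihood from a real group variance is often below the penalty, so the criterion prefers the model without it. The analysis then treats grouped students as independent, and the standard error of any contrast that involves a grouped arm is too small.

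The contrasts between G4H and the other active arms are hit hardest, because both sides are clustered. They carry the article's hypothesis that G4H reduces loneliness for longer than the other interventions do.

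**Working it through.** **Inputs from the article.** Arm sizes at the freeze: G4H 155, SPG 125, TBWS 216, controls 203 (total 699). Group sizes: 6.5 (midpoint of 4–9), 11 (midpoint of 10–12), 5, and 1 for controls. With full groups this implies about 155/6.5 ≈ 24, 125/11 ≈ 11 and 216/5 ≈ 43 groups, 78 in all. Anticipated attrition: 35%.

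**Assumption.** The ICC is not in the documents; values from 0.02 to 0.10 are shown.

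**1. The plan's own figure.** The article states at least 95% power for f = 0.20 with 600 students, multiple comparisons and 35% attrition, so N = 390. For the between-groups test in repeated measures ANOVA, λ = f²·N·m/(1+(m−1)ρ). Assuming m = 4 measurements and ρ = 0.5, λ = 0.04×390×4/2.5 = 24.96. Power is 99.3% at α = 0.05 and 96.2% at α = 0.05/6. The stated figure therefore reproduces without any allowance for clustering, so the sample size does not show that the group level was provided for.

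**2. Size of the error if groups are ignored.** Design effect: DEFF = 1+(m−1)·ICC, with m now the group size. At ICC 0.05: G4H 1+5.5×0.05 = 1.275, SPG 1.50, TBWS 1.20, controls 1. For two arms of equal size, true SE / naive SE is r = √((DEFF₁+DEFF₂)/2), and the actual two-sided error is 2·P(Z > 1.96/r). Example, G4H versus SPG at ICC 0.05: r = √((1.275+1.50)/2) = 1.178, which gives 9.6%.

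| ICC | G4H vs control: r, error | G4H vs TBWS: r, error | G4H vs SPG: r, error |
|---|---|---|---|
| 0.02 | 1.03, 5.6% | 1.05, 6.1% | 1.07, 6.8% |
| 0.05 | 1.07, 6.6% | 1.11, 7.8% | 1.18, 9.6% |
| 0.10 | 1.13, 8.3% | 1.21, 10.7% | 1.33, 14.1% |

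With the actual sizes 155 and 125, r² for G4H versus SPG at ICC 0.05 is (1.275/155+1.5/125)/(1/155+1/125) = 1.40, and the error is 9.8%. These are full group sizes. If 35% attrition shrinks every group, G4H versus SPG falls to 7.8% (ICC 0.05) and 10.6% (ICC 0.10).

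**3. How often the criterion drops a real group effect.** AIC keeps the group variance only if twice the log-likelihood gain exceeds 2. BIC asks for more than ln N, which is ln 699 = 6.55 at full size. Simulation: four arms at the freeze sizes, one outcome per student (such as a change score), maximum likelihood fits with and without a group effect, 1000 runs per setting. Ranges run from no attrition to 35% attrition.

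| ICC | AIC drops | BIC drops |
|---|---|---|
| 0.02 | 84–89% | 98% |
| 0.05 | 49–72% | 86–94% |
| 0.10 | 11–35% | 39–72% |

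A repeat of the simulation gives 53–72% and 86–95% at ICC 0.05, and 10–36% and 40–72% at ICC 0.10.

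**4. Type I error after selection, G4H versus SPG, same simulation.**

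| ICC, attrition | Group kept | After AIC | After BIC | Group ignored |
|---|---|---|---|---|
| 0.05, none | 5.5% | 6.5% | 8.3% | 8.8% |
| 0.05, 35% | 6.7% | 7.8% | 8.8% | 9.2% |
| 0.10, none | 5.7% | 6.5% | 8.9% | 15.9% |
| 0.10, 35% | 6.0% | 6.8% | 8.5% | 10.6% |

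Monte Carlo error is √(0.05×0.95/1000) ≈ 0.7 points. The repeat gives about 6–7% after AIC and 6–9% after BIC. For G4H versus control, the error after selection at these ICCs is 5.4–7.3% with AIC and 6.1–7.8% with BIC, against 4.9–7.0% with the group kept.

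**The case against.** The strongest reply is that the article never says the group effect will be put to the test. Model structure could mean the time trend, random slopes or residual covariance, where information criteria are a sound tool, and a separate analysis plan may fix the levels. That stands as a limit: the problem arises only if the delivery-group term is among the candidates. But the rule as written covers the whole structure, and the preceding sentence gives hierarchy as the reason for the model.

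The second reply is that the harm limits itself. At ICC 0.02, where the effect is dropped most often, the true standard error is at most about 8% above the naive one. At ICC 0.10 AIC mostly keeps the effect. This also stands, and is why the error after selection stays below 10% in the settings shown. Both simulations use one outcome per student, not the full repeated-measures model.

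Three stronger readings are tempting:

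- A reader might infer that the rule will usually remove the group effect. That depends on the criterion and on an ICC that the documents do not give, and it fails for AIC at ICC 0.10.
- A reader might take the 10–14% error for G4H versus SPG as the effect of the rule. Those figures assume that groups are ignored in every analysis.
- A reader might infer that the stable unit treatment value assumption makes standard errors too small. It does not. It concerns interference and the definition of the effect, the article invokes it for selection into arms, and interaction within a delivered group can be read as part of the treatment.

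**Conclusion.** The point holds as a weakness in a stated rule. The design puts three arms in groups and one in none, and the rule does not protect that level from data-driven selection.

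If the group term is selected this way, a real one is dropped in about 50–72% (AIC) or 86–95% (BIC) of trials at an assumed ICC of 0.05, and in about 10–36% or 39–72% at 0.10. Type I error for G4H versus SPG then becomes roughly 6–7% with AIC (7.8% in one setting, where the model with the group kept also read 6.7%) or 6–9% with BIC. It would be about 10% (ICC 0.05) to 14% (ICC 0.10) at full group sizes if groups were ignored altogether. G4H versus control is less affected.

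The inflation is modest, but it falls mainly on the comparisons between active arms and is avoidable. The change should be made before the analyses are run.

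**What to change.** State in the analysis section that:

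1. A delivery-group random effect is kept in arms 1–3 whatever AIC or BIC says, with none in controls (a partially nested model).
2. Information criteria are used only for the time trend and the student-level covariance.
3. The weighted and doubly robust estimators use standard errors clustered on delivery group, or a bootstrap that resamples groups.

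Small-sample degrees of freedom are worth adding, since SPG has only about 11 groups. One optional sentence could say that interaction within a delivered group is treated as part of the intervention.

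The cost is slightly wider intervals and some data work. Group identifiers must be linked to the outcome data. Table 1 lists no such identifier, and TBWS peer groups run on the course platform while the week 3 and follow-up data are collected only in REDCap, so the linkage should be confirmed first.
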